| --- | --- |

1. **Study design**

| **3.1**  **a. General description of the study design** | This research project will use the data infrastructure Extramural Leiden Academic Network (ELAN).  ELAN provides access to and the use of pseudonymized healthcare data from various cooperating partners such as healthcare data of general practitioners. The study period concedes 2014-2024.  ***Question***  Is antibiotic use associated with increased risk for urinary tract infection in adults?  Further explorations will be done to what extent the increased UTI risk of antibiotic use holds for:   - Different antibiotics or antibiotic classes - Men versus women - Post- versus Premenopausal women - Indication for antibiotic treatment (excluding UTI’s)   A self-controlled cases series (SCCS) design will be employed to establish the risk for developing an UTI within 3 months after antibiotic treatment compared to patients with an UTI who did not receive an antibiotic treatment. With the SCCS design, patients will be their own control.  The primary endpoint is risk of a UTI within 3 months after initiation of antibiotic treatment computed as an odds ratio.  An antibiotic treatment is defined as the exposure. An UTI between 2 weeks and 3 months after antibiotic treatment is defined as an event. The first 2 weeks after start of the treatment, patients are still somewhat protected by the antibiotic use against a new infection. And if a new antibiotic treatment is needed within 2 weeks after start of treatment, this is considered as treatment failure of the initial treatment.  Descriptive analysis will be performed for exposures, outcomes and covariables for the whole population of analysis and stratified by antibiotic use or not.  Multivariable logistic regression analysis will be performed to assess whether there is an association of antibiotic use with developing a UTI within 3 months after initiation of treatment. First a crude model will be used followed by confounder adjusted models. Confounders are season variability (Winter, spring, summer and autumn) and risk factors for UTI and selected based on theory or literature (Tj VanderWeele 2019). Risk factors are a history of an UTI, urine incontinence, urolithiasis, pregnancy, urine catheter, anatomical / functional abnormality urinary tract, immunocompromising comorbidities such as HIV/AIDS ,Type 2 Diabetes Mellitus.  **Subgroup analysis**  Subsequently, subgroup analysis will be performed to examine whether the association differs upon specific type of antibiotic treatment. For each subgroup, we will calculate an odds ratio for an UTI after antibiotic treatment. Subgroups are antibiotic(group)s, gender and age, type of infection and social determinants .  *Most used antibiotic(group)s in primary care*:   - Amoxicillin - Amoxicillin/clavulanic acid - Flucloxacillin - Tetracyclines - Macrolides - Fluoroquinolones - Trimethoprim - Co-trimoxazole - Fosfomycin - Nitrofurantoin   *Type of infection*   - All infections - UTI - non-UTI (all other infections)   *Gender and age*   - Men - Premenopausal women, defined as < 50 years of age - Postmenopausal women, defined as ≥ 50 years of age   *Social determinants*   - Socio-economic status (SES) - Migrant background |

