| --- | --- |
| **3.2**  **a. When will the study be conducted?**  **b. What is the intended end date of the study?** | The research will be performed as part of a MSc. Internship ([name]) in the period between February 2025 and June 2025.  Month 1 – Literature research, writing the introduction, first part of data preparation.  Month 2 – Writing the introduction and methodology, second part of data preparation.  Month 3 – Completing the introduction, methodology and data preparation, start of data analysis.  Month 4 – Completing the data analysis and writing the results.  Month 5 – Writing the report, focusing on the discussion.  The end date is July 2025. |
| **3.3**  **Does the study involve exclusively existing (patient) data (retrospective) and not data yet to be generated (prospective)?** | This study includes already existing data only, and is thus retrospective (see also 3.1). |
| **3.4**  **What type of data will be used for the research?** | Pseudonymized routine care patient data from GP practices participating in ELAN. |
| **3.5**  **If information from patient records is used: describe what type of information is involved.** | The dataset from ELAN contains data over a period of 10 years and includes:   - Number of all included patients in ELAN per year - All patients with an UTI   - ICPC code U70, U71, including subcodes   - Date of registration with GP office - Antibiotic prescriptions ATC J01 for all patients with an UTI   - Corresponding medical diagnosis with the antibiotic prescription by ICPC code   - Details on the antibiotic prescription (name of antibiotic, dose and duration) - Characteristics of included patients   - Year of birth   - Year of death   - Sex   - Referral to urologist for recurrent UTIs   - Risk factors for an UTI     - History of UTI ICPC code U70, U71     - Urine incontinence ICPC code U04     - Urolithiasis ICPC code U95     - Urine catheter ICPC code U28     - Anatomical / functional abnormality urinary tract ICPC code U85     - Type 2 Diabetes Mellitus ICPC code T90.02     - Prostate hypertrophy ICPC codes Y06, Y85     - Medication use for miction problems with ATC codes     - G04BD     - G04C     - Social economic status     - Migrant background |
| **3.6**  **To which time period do the data relate?** | The period between 2014 and 2024 |

1. **Data storage and privacy**

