| **6.1**  **a. Primary outcome**  **b. Secondary outcome** | ***Primary outcome***  What is the association of antibiotic use for any infection with risk for urinary tract infection in adults?   - Odds ratio for an UTI after antibiotic use in the preceding 3 months   - Per infection group, antibiotic for     - All infections     - An UTI     - An infection expect UTI’s   - Per antibiotic (group)   - Per patient group     - Men     - Women < 50 years of age     - Women ≥ 50 years of age   - Social determinants     - SES     - Migrant background   - Combinations of each subgroup   ***Secondary outcome***   - Hazard ratio for an UTI after antibiotic use in the preceding 3 months   - Per infection group, antibiotic for     - All infections     - UTI     - non-UTI   - Per antibiotic group   - Per patient group     - Men     - Women < 50 years of age     - Women ≥ 50 years of age   - Social determinants     - SES     - Migrant background   - Combination of each subgroup - Incidence of an UTI per month |
| --- | --- |
| **6.2**  **a. Statistical analysis primary outcome**    **b. Statistical analysis secondary outcome** | ***Primary outcome***  The Odds ratio for an UTI after antibiotic treatment the preceding 3 months will be calculated through a logistic regression model.  Risk factors and season variability are defined as confounders in this logistic regression model. Risk factors are a history of an UTI, urine incontinence, urolithiasis, pregnancy, urine catheter, anatomical / functional abnormality urinary tract and Type 2 Diabetes Mellitus. An Odds ratio for an UTI will be attributed to each confounder based on a critical literature appraisal.  ***Secondary outcome***  Cox proportional hazard regression models will be used to examine the associations between an UTI after antibiotic treatment the preceding 3 months.  Survival time (in days) was defined as the period between 14 days after the start of the antibiotic treatment and an UTI. The hazard ratio will be adjusted with the previous described confounders (see primary outcome).  The incidence of each UTI will be calculated for each month during 10 years to examine the season variability. |

1. **Appendices and references**

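### The confounder lists in Protocol 3.1 and 6.2 do not match the variables extracted in 3.5: prostate hypertrophy and miction medication enter no model, and immunocompromise and pregnancy have no code

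*Protocol*

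**What the plan says.** Three places in the Protocol bear on adjustment.

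- **Section 3.5 (data to be extracted).** Under its list of UTI risk factors it gives "Prostate hypertrophy ICPC codes Y06, Y85" and "Medication use for miction problems with ATC codes" G04BD and G04C. As a separate line it gives "Anatomical / functional abnormality urinary tract ICPC code U85". History of UTI, incontinence, urolithiasis, catheter and type 2 diabetes are also coded there.
- **Section 3.1 (design).** It defines the confounders as season plus risk factors for UTI, chosen on theory or literature, and then lists them: "Risk factors are a history of an UTI, urine incontinence, urolithiasis, pregnancy, urine catheter", then anatomical or functional abnormality, and finally "immunocompromising comorbidities such as HIV/AIDS ,Type 2 Diabetes Mellitus".
- **Section 6.2 (statistical analysis).** For the primary logistic model it repeats most of that list, ending "urolithiasis, pregnancy, urine catheter, anatomical / functional abnormality urinary tract and Type 2 Diabetes Mellitus". The secondary Cox model takes its confounders from this list.

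Section 6.1 makes men a separate patient group for both the odds ratio and the hazard ratio.

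**The concern.** By the rule in 3.1, a UTI risk factor is a candidate confounder. The protocol itself calls prostate hypertrophy and miction medication UTI risk factors and requests the data, but gives them no place in any model. If men with these problems both receive more antibiotics and have more UTIs, the estimates in men carry that confounding although the data to reduce it are in hand. Section 2.1 says that, to the authors' knowledge, no study has addressed men, so the result in men may well be read on its own.

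The reverse gap matters too. Section 3.1 tells the reader that immunocompromise is controlled, 6.2 says nothing of it, and 3.5 requests no data for it. Because 3.5 defines the data request, a later analysis plan cannot adjust for a variable that was never requested.

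**Working it through.** **Step 1. Compare the lists item by item.**

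| Item | Coded in 3.5 | Confounder in 3.1 | Confounder in 6.2 |
|---|---|---|---|
| History of UTI | yes (U70, U71) | yes | yes |
| Incontinence | yes (U04) | yes | yes |
| Urolithiasis | yes (U95) | yes | yes |
| Catheter | yes (U28) | yes | yes |
| Anatomical or functional abnormality | yes (U85) | yes | yes |
| Type 2 diabetes | yes (T90.02) | yes | yes |
| Prostate hypertrophy | yes (Y06, Y85) | **no** | **no** |
| Miction medication | yes (G04BD, G04C) | **no** | **no** |
| Immunocompromise (HIV/AIDS etc.) | **no** | yes | **no** |
| Pregnancy | **no** | yes | yes |

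Socio-economic status and migrant background also stand in 3.5 and in neither confounder list, but they have a stated use as subgroups. Season needs no code, since it follows from dates.

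**Step 2. Could the omitted items be covered by another term?** Section 3.5 codes anatomical or functional abnormality as U85 alone and lists prostate hypertrophy and miction medication on separate lines. They are therefore not inside that term.

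**Step 3. Could type 2 diabetes stand for immunocompromise?** The wording in 3.1 allows diabetes to be read as one example of an immunocompromising condition, and diabetes is coded. HIV/AIDS, which 3.1 names, still has no code in 3.5.

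**Step 4. Size, as an illustration only.** The protocol gives no prevalence or effect for these factors, so every input here is an assumption: prostate or voiding problems in p0 = 15% of unexposed and p1 = 20% to 30% of exposed male observations, and a UTI risk ratio RR of 1.5 to 3. With no true effect of antibiotics and no adjustment, the observed ratio is

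[1 + p1(RR − 1)] / [1 + p0(RR − 1)]

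- p1 = 0.20, RR = 1.5: 1.10 / 1.075 = 1.02
- p1 = 0.30, RR = 1.5: 1.15 / 1.075 = 1.07
- p1 = 0.20, RR = 3: 1.40 / 1.30 = 1.08
- p1 = 0.30, RR = 3: 1.60 / 1.30 = 1.23

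The formula compares different people and takes no account of the related factors that the models do include.

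**The case against.** The strongest objection is the design. Section 3.1 announces a self-controlled case series in which patients serve as their own controls. In such an analysis a condition that is stable over a person's observation time cancels, and leaving it out of the model does no harm. This stands in part: if a true within-person analysis were run, the bias would be smaller. But 6.2 specifies logistic and Cox regression with patient-level risk factors as covariates and describes no conditional or within-person model. Prostate disease can also begin, and miction medication can start or stop, within a study period of about ten years.

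Second, a reader might infer that the models in men contain no voiding-related variable at all. The text does not support that. Incontinence, catheter and U85 are in both lists, and together with history of UTI they would absorb part of the confounding. What is missing is the prostate-specific information and the miction medication.

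Third, a reader might infer that the model in 3.1 cannot be fitted. That goes too far: only the immunocompromise term, and pregnancy by the same reasoning, cannot be filled from the listed data. On immunocompromise, 6.2 agrees with 3.5 and 3.1 is the outlier.

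Fourth, extracting a variable without modelling it is not in itself an error. Section 3.1 plans a description of covariables, and referral to a urologist is likewise extracted without a model role. Here, however, the protocol labels the two items as UTI risk factors and defines confounders as UTI risk factors, so its own rule points to including them.

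**Conclusion.** The inconsistency is in the current text and does not depend on any assumption. Two extracted UTI risk factors are absent from both confounder lists; one listed confounder is in 3.1 only and has no code; pregnancy is in both lists and has no code. If 6.2 is followed as written, prostate hypertrophy and miction medication are left uncontrolled in the models in men, apart from what the related covariates pick up.

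The size of the resulting bias is unknown. The range 1.02 to 1.23 rests wholly on assumed prevalences and risk ratios, ignores the other adjustments, and is a between-person contrast that may not carry over to a dataset whose antibiotic prescriptions are requested only for patients with a UTI. A reader might take 1.23 as an estimate of the bias in men; the document gives no basis for that, and the low end is negligible. The point is worth correcting because the fix is nearly free, not because the study fails without it.

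**What to change.** 1. Add prostate hypertrophy (Y06, Y85) and miction medication (G04BD, G04C), measured before the exposure or reference date, to the confounder lists in 3.1 and 6.2 for the models in men.
2. For immunocompromise, either add codes to 3.5 and keep the term in both 3.1 and 6.2, or delete it from 3.1 and state that it is unmeasured.
3. Add a pregnancy/delivery code to 3.5. The event exclusions in 5.2 for pregnancy and the three months after birth need it as well.
4. Use one identical list in 3.1, 3.5 and 6.2, with a code for every clinical item.

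The prostate and miction variables are already in the extraction, so they cost only a few model terms. Immunocompromise, if kept, and pregnancy each need a few extra codes in the data request.

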| **4.10**  **If coding takes place: when will coding occur, by whom, and in what manner?** | Coding is done by STIZON and CBS |
| **4.11**  **Has a notification of the intended data processing been submitted via:**  <https://www.albinusnet.nl/weten-en-regelen/juridische-zaken/privacy/meldenverzamelenonderzoeksdata/>**?** | Yes |
| **4.12**  **If applicable: where will the coded data be stored, and who will have access to the coded data?**  **If applicable: where will the uncoded data be stored, and who will have access to the uncoded data?** | The coded data is stored, and a specific research folder assigned to the department disk (I: \) of PHEG. Only the researchers involved ([name] and [name]) and the PHEG data manager have access to this folder.  There is no storage of uncoded data. |
| **4.13**  **What technical and organizational measures have been taken to prevent loss, theft, or unauthorized use of the research data? For example, is a data safe being used?** | The data never physically leaves the research folder of the LUMC or the remote access CBS environment and see 4.12. |
| **4.14**  **By whom is the code key managed?** | STIZON. |
| **4.15**  **Will (research) data be shared with another institution(s) within the Netherlands and/or the EU?** | No. |
| **4.16**  **a. Will (research) data be shared with another institution/organization outside the EU?**  **b. Will the relevant patients be asked for consent to share their personal data with a country outside the EU?** | No.  Not applicable. |
| **4.17**  **How long will the (research) data be retained? If the data will be kept for longer or shorter than the standard retention period of 15 years, please explain why.** | After processing, the research data is returned to ELAN in accordance with the data transfer agreement. The LUMC department PHEG will keep the research data for 15 years. |

1. **Research population**

| **5.1**  **Inclusion criteria** | Adults patients 18 year and older with an acute UTI and registered at an GP office for a least 1 year |
| --- | --- |
| **5.2**  **Exclusion criteria** | Patients younger than 18 years of age.  Patients with antibiotic prophylaxes  UTIs are excluded as an event if   - During pregnancy - within 3 months after giving birth - within 1 year prior to an UTI (wash-our period) |

1. **Statistical analysis**

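### Extract and study period both start in 2014 with no look-back, so early-2014 exposure and 2014 wash-out and UTI-history status are incompletely ascertained (minor, cheap to fix)

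*Protocol*

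**What the plan says.** - **Dates.** Section 3.1: "The study period concedes 2014-2024". Section 3.6, on the data: "The period between 2014 and 2024". Section 3.5: "The dataset from ELAN contains data over a period of 10 years and includes".
- **Exposure.** Section 6.1 defines the primary measure as "Odds ratio for an UTI after antibiotic use in the preceding 3 months". Section 3.1 sets the risk window: "An UTI between 2 weeks and 3 months after antibiotic treatment is defined as an event".
- **Wash-out.** Section 5.2 excludes a UTI as an event if "within 1 year prior to an UTI (wash-our period".
- **UTI history.** Sections 3.1 and 6.2 list it as a confounder. Section 3.5 takes it from the ICPC codes U70 and U71, the same codes that identify the outcome.
- **Registration.** Section 5.1 requires patients to be "registered at an GP office for a least 1 year".
- **Incidence.** Section 6.2: "The incidence of each UTI will be calculated for each month during 10 years to examine the season variability".

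The protocol mentions no run-in, look-back year or earlier data. No SAP was available.

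**The concern.** Each backward-looking rule needs records from before the UTI that it classifies. At the start of 2014 those records are not in the extract. Three things follow.

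- A UTI in February 2014 after a course started in December 2013 has no visible exposure and would be classed as unexposed.
- A UTI in June 2014 that follows one in September 2013 would pass the 1-year wash-out and be coded as having no UTI history. The same sequence one year later would be caught.
- The registration criterion does not close the gap. It counts time on the practice list, not time covered by the extract. A patient registered since 2005 meets it on 1 January 2014 with no earlier data.

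At stake are a small bias of the odds ratio toward 1, different eligibility in 2014 from later years, a confounder whose measurement improves with calendar time, and possibly a false decline at the start of a series meant to show seasonality.

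**Working it through.** The protocol states no event count, power or sample size, so there is no figure to reproduce. The check is date arithmetic plus two illustrations with assumed inputs.

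**1. Calendar time affected.** 2014 to 2024 inclusive is 11 × 12 = 132 months (4018 days).

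- Exposure: 3/132 = 2.3%.
- Wash-out and history: 12/132 = 9.1%.
- If the period is read as 10 years (120 months, 3652 days): 3/120 = 2.5% and 12/120 = 10%.

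**2. Share of the exposure window unseen.** Take the window as 14 to 91 days before the UTI, 77 days long. For a UTI x days after 1 January 2014 (x < 91), the unseen part is 91 − max(14, x) days. Summed over x = 0 to 90:

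14 × 77 + (77 × 78)/2 = 1078 + 3003 = 4081

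The average unseen share is 4081/(91 × 77) = 0.582. Over the whole study this equals 4081/77 = 53 days of fully missing window: 53/4018 = 1.3%, or 53/3652 = 1.5%.

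**3. Effect on the odds ratio.** Assumptions: true OR 2.0; exposure prevalence p0 of 10% or 20% in the comparator; the same fraction m of true exposures missed in both groups; an unmatched odds ratio. Then p1 = 2p0/(1 + p0), and the observed OR is the ratio of the odds of p1(1 − m) and p0(1 − m).

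| p0 | p1 | whole study, m = 0.013 | first 91 days only, m = 0.582 |
|---|---|---|---|
| 0.10 | 0.182 | 2.00 | 1.89 |
| 0.20 | 0.333 | 1.99 | 1.77 |

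**4. Wash-out, if it governs the monthly incidence.** Read the rule as no UTI in the preceding year. Give each woman a constant rate λ, gamma-distributed with mean μ = 0.117 per year (the 117 per 1000 women in section 2.1) and shape k from 0.3 to 1.0 (assumed). With look-back L years, the rate of UTIs that pass is

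q(L) = E[λ exp(−λL)] = μ(1 + μL/k)^−(k+1)

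Inflation is q(L)/q(1), with L taken at mid-month (January: 0.5/12 = 0.042).

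- k = 0.3: (1.39/1.01625)^1.3 = 1.50
- k = 0.5: (1.234/1.00975)^1.5 = 1.35
- k = 1.0: (1.117/1.004875)^2 = 1.24

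The same formula gives 1.12 to 1.24 in June, about 1.01 in December, and a 2014 mean of 1.12 to 1.23.

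**5. Does the wash-out do anything in 2014?** Yes. In the same model 10-20% of 2014 UTIs still fail because of an earlier UTI recorded that year. With a full year of look-back, 20-35% would fail. Only a patient's first recorded 2014 UTI goes unchecked.

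**6. UTI history.** Under the same reading, an admitted 2014 UTI has no recorded UTI in the preceding year, and the extract holds nothing earlier. If history comes only from this extract, it is recorded as absent for every admitted 2014 event. From 2015 the available look-back lengthens each year.

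**The case against.** The strongest reply has four parts.

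- **The primary result hardly moves.** This stands. Only UTIs in about the first 91 days are affected, on average 42% of their window is still visible, and the overall odds ratio changes in the third significant figure. A reader might infer that early UTIs in general are classed as unexposed and that the primary estimate is materially biased. The dates and the arithmetic do not support that.
- **The incidence artefact rests on an unstated premise.** This also stands. Section 5.2 excludes UTIs as events in the association analysis, while section 6.2 speaks of each UTI when it describes the monthly series. If all UTIs are counted, there is no inflation and no decline. Even if the wash-out applies, one inflated January among 11 raises the average January by only about 24/11 = 2% to 50/11 = 4.5%.
- **The wash-out wording is garbled.** Taken literally, section 5.2 removes a UTI that precedes another within a year, which would put the incomplete ascertainment at the end of 2024. The term wash-out makes the backward reading the natural one, but the point depends on it.
- **A run-in may be intended.** 2014 to 2024 inclusive is 11 calendar years and the incidence series covers 10, which would fit a 2014 run-in. However, section 3.5 gives the dataset the same length of 10 years, so no year is left over and the text does not establish one. An SAP could set the first date of analysis, but it could not create 2013 records, and a 2015 start would differ from the study period in section 3.1.

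A reader might also infer that all 2014 UTIs pass the wash-out by default. They do not: later 2014 UTIs can fail on the first.

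**Conclusion.** The point holds, at minor severity. The extract and the study period start together, no look-back is stated, and the registration criterion does not provide one. The stated exposure rule cannot be applied fully in about the first 3 months of 2014, nor the wash-out and history rules during that year.

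For the overall odds ratio the consequence is negligible under the stated assumptions. For the monthly incidence it is conditional: roughly 1.2 to 1.5 times too high in January 2014 if the wash-out applies, and nil if every UTI is counted. That range depends on the assumed gamma shape and on the rate in women. It is not an upper bound, because the model implies that only 7-15% of UTIs recur within 4 months, against the 20-30% of women within 3-4 months cited in section 2.1. For UTI history the problem does not depend on how incidence is defined and continues beyond 2014, because look-back grows with calendar time.

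**What to change.** 1. In sections 3.1 and 3.6, state that 2014 serves only as look-back and that events and exposed time are counted from 1 January 2015. If the extract runs to the end of 2024, this leaves 10 full calendar years, matching the 10 years in section 6.2. Alternatively, extract 2013 as look-back and keep the 2014 start.
2. In section 5.2, reword the wash-out so that its direction is clear. In section 6.2, say whether it governs the monthly incidence. If it does, use the same start date there.
3. Define UTI history over a fixed look-back. It must be longer than the wash-out: over exactly one year, every admitted UTI has no history by construction. A longer window needs earlier records (for example 2013 together with a 2015 start) or a later start, and comparable coverage for patients who register during the study.

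The cost is a few sentences. A 2015 start needs no new data and gives up about 9% of calendar time (12/132), and roughly that share of events, from a database of all adult ELAN patients. Extracting 2013 loses no study time but requires a wider data request.

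### Section 5.2 drops UTIs in pregnancy and the 3 months after birth as events but not the matching time and antibiotic courses, pregnancy also stays a covariate, and the listed extract supports neither

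*Protocol*

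**What the plan says.** Section 5.2 first excludes whole patients (by age, and for antibiotic prophylaxis). It then moves to the level of the outcome: "UTIs are excluded as an event if" they fall in pregnancy or "within 3 months after giving birth". It does not mention follow-up time or antibiotic courses in that period.

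Section 3.1 makes no exception for such courses. It says "An antibiotic treatment is defined as the exposure" and "An UTI between 2 weeks and 3 months after antibiotic treatment is defined as an event". The design is self-controlled: "With the SCCS design, patients will be their own control".

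Section 6.2 lists pregnancy among the adjustment variables, as 3.1 does: "Risk factors are a history of an UTI, urine incontinence, urolithiasis, pregnancy, urine catheter". It continues: "An Odds ratio for an UTI will be attributed to each confounder based on a critical literature appraisal". The same confounders are carried into the Cox model.

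Section 3.5 itemises the data. Under "Characteristics of included patients" it gives ICPC codes for most of the other risk factors (incontinence, urolithiasis, catheter, urinary tract abnormality, type 2 diabetes). It lists no pregnancy code, start of pregnancy or delivery date.

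**The concern.** Time in which no event can count should not sit in the risk set. If it does, each antibiotic course given in it adds exposed time that cannot be followed by an event, and the remaining days add unexposed time of the same kind. The two cancel only if exposure is equally frequent inside and outside the window. Otherwise the ratio moves. The movement falls essentially on women under 50, so it would also enter the planned comparison of pre- and postmenopausal women.

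Two other parts of the plan do not fit with the exclusion. A pregnancy covariate has no events left to inform it, yet it is to carry an odds ratio from outside. And both the exclusion and the covariate need dates that the listed extract does not contain.

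**Working it through.** The protocol gives no figure on this point, so there is nothing to reproduce. The question is how far the ratio can move.

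**Inputs.** From the protocol: about 10 years of data (3.5, 3.6), a 3-month window after birth (5.2), and women under 50 as a subgroup (3.1, 6.1). Assumed: 9 months of pregnancy, so the window is 9 + 3 = 12 months; exposed share of time outside the window e0 = 10%; exposed share inside it e1 = 0.5 to 2 times e0; true rate ratio 1.5. One pregnancy in 10 years gives a window share f = 12/120 = 10%. One in 5 observed years gives f = 12/60 = 20%.

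**Branch A: pregnancy dates exist, events removed, time kept, no pregnancy term.** The true ratio is multiplied by

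factor = [e0(1-f) / (e0(1-f) + e1·f)] / [(1-e0)(1-f) / ((1-e0)(1-f) + (1-e1)·f)].

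For f = 10%:

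- e1 = 20%: (0.09/0.11) / (0.81/0.89) = 0.818/0.910 = 0.90, so 1.50 becomes 1.35.
- e1 = 10%: factor 1.00, no bias.
- e1 = 5%: (0.09/0.095) / (0.81/0.905) = 0.947/0.895 = 1.06, so 1.50 becomes 1.59.

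For f = 20%:

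- e1 = 20%: (0.08/0.12) / (0.72/0.88) = 0.667/0.818 = 0.82.
- e1 = 5%: (0.08/0.09) / (0.72/0.91) = 0.889/0.791 = 1.12.

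*Whole stratum*, approximated as the share of women affected times (factor - 1), with 20-40% affected (assumption):

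- 10 years: 0.2 to 0.4 × (-10%) = -2% to -4%; 0.2 to 0.4 × (+6%) = +1.2% to +2.4%.
- 5 years, 40% affected: 0.4 × (-18%) = about -7%; 0.4 × (+12%) = about +5%.

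*Check by logistic regression* on 400,000 simulated records (f = 10%, e1 = 20%, e0 = 10%, risk 3% exposed and 2% unexposed outside the window): odds ratio 1.40 with the time kept and 1.56 with it removed. The ratio 1.40/1.56 = 0.90 agrees with the formula.

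**Branch A with the pregnancy covariate.** The effect depends on how the covariate enters.

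- *Freely estimated.* A stratum with no events drops out. When the term covers the whole window, the simulated odds ratio is 1.56, the same as removing the time. If the term covers pregnancy only, the 3 months after birth remain: f = 0.25/(10 - 0.75) = 2.7%, and 1.50 becomes 1.46 (e1 = 20%) to 1.52 (e1 = 5%).
- *Fixed at a literature value.* With an odds ratio of 2 (assumption) applied to the whole window, the window's time counts double. For e1 = 20%: (1.5 × 0.09/0.13) / (0.81/0.97) = 1.24. For e1 = 5%: (1.5 × 0.09/0.10) / (0.81/1.00) = 1.67. Both lie further from 1.50 than without the term.

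**Branch B: no pregnancy dates.** No event can be removed and no covariate built, so the Branch A bias cannot arise. Pregnancy confounds instead. With a doubled UTI rate in the window (assumption) and f = 10%:

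- e1 = 20%: [1.5 × (0.09 + 2 × 0.02)/0.11] / [(0.81 + 2 × 0.08)/0.89] = 1.773/1.090 = 1.63.
- e1 = 5%: [1.5 × (0.09 + 2 × 0.005)/0.095] / [(0.81 + 2 × 0.095)/0.905] = 1.579/1.105 = 1.43.

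**With the time removed.** Taking out the window's time and courses along with its events returns 1.50 in every Branch A scenario.

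**The case against.** The strongest reply is that 5.2 is a short eligibility list. It says which UTIs do not count and is silent on person-time. Censoring and risk windows are often set in an analysis plan, which is not at hand. This stands in part: retention of the time is the natural reading of an exclusion worded for events only, but it is not stated.

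Second, pregnancy is an adjustment variable, and a freely estimated term would remove most of the bias. That is correct as arithmetic. But 6.2 speaks of odds ratios attributed from the literature, and if these are used as fixed values the bias grows.

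Third, 3.5 may not be exhaustive: the immunocompromising comorbidities named in 3.1 are also absent from it. So the gap holds for the extract as listed and no further. The diagnosis linked to each prescription could flag some treated pregnancies, but it would not date the start of pregnancy or the birth.

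Fourth, the factors are for a person-time rate ratio, while the primary measure is a logistic odds ratio whose unit of analysis the protocol does not settle. They show the order of size and are not a prediction.

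A reader might infer that the estimate for women under 50 is biased, and that the retained time and the missing data add up. The documents support neither. No antibiotic rate in pregnancy is given, so neither the presence nor the direction of a bias is established. The two problems are alternatives: without pregnancy dates no event is removed, so retained time does no harm of this kind.

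**Conclusion.** The point holds as an inconsistency among 5.2, 3.1/6.2 and 3.5, with a conditional effect on the estimate for women under 50.

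If pregnancy dates are available, the event-only exclusion can shift that estimate either way. Over 10 years the factor is about 1.06 to 0.90 per affected woman, or roughly +2% to -4% for the stratum. This rests on an exposure ratio of 0.5 to 2, 10% of other time exposed, one pregnancy per affected woman and 20-40% of women affected, all of them assumptions. The 5-year figures, about +5% to -7%, are an outer case. Any distortion of the comparison between pre- and postmenopausal women is equally conditional.

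If the dates are not available, the exclusion cannot be applied and pregnancy is an unmeasured confounder.

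The size is modest under these assumptions, but neither branch is sound as written. The gap in the extract is the more pressing part, because an item left out of the extraction is hard to recover later.

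**What to change.** 1. In 3.5, add pregnancy and delivery items with dates.
2. In 5.2, replace the event exclusion for pregnancy and the 3 months after birth with a time exclusion. All follow-up time and exposure windows from the start of pregnancy to 3 months after birth leave the analysis, and the woman re-enters afterwards. State how a risk window that crosses either boundary is treated.
3. In 3.1 and 6.2, drop pregnancy from the confounder list. Once that time is out, the covariate is redundant, and no literature odds ratio is needed for it.

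The cost is one more data item, a few sentences, and a slight loss of person-time in women under 50.
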